### Study setting

The study is currently being conducted at The Ohio State University (OSU) in Columbus, Ohio (OH) and Yale Cancer Center in New Haven, Connecticut (CT). The research protocol has been approved by the OSU Institutional Review Board (IRB) and Yale has ceded review to this board as the single IRB for the multisite clinical trial. At OSU, participants are recruited from the Stephanie Spielman Comprehensive Breast Center (SSCBC) oncology practice as well as from the greater central OH community. At Yale, participants are recruited from the Yale Center for Breast Cancer (CBC) within the Smilow Cancer Center oncology hospital network as well as from the greater south central, CT and northern New York City, New York communities. Consent is obtained in a quiet and private setting prior to research activity either electronically, via REDCap (Research Electronic Data Capture, Nashville, TN), or using a paper version which is stored securely in a locked cabinet within a secure research-dedicated space at the host institutions. Assessments (i.e., screening, repeated baseline, midpoint, post intervention, and 1-month follow-up assessments) are performed in an outpatient care clinic setting or within the volunteer’s home environment, as preferred by the survivor. The EXP intervention is performed in a group setting of no more than 15 survivors at a time with their invited partners. The SOC portion of the CON intervention is performed by participants in their own home environment. Participants are compensated $20 per in-person assessment session that does not involve interventional instruction, with an additional $20 compensated for sessions that require sensors to be applied to the skin (potential total of up to $280 for participation in all assessments).

### Eligibility criteria

The eligibility criteria of this study follows the criteria described in Lantis et al. (2023) (46). Briefly, participants are eligible for this study if they are 40 years old or older, diagnosed with BC (all stages), experiencing CIN (European Organization for Research and Treatment of Cancer, Chemotherapy-Induced Peripheral Neuropathy outcome measure (CIPN-20) sensorimotor score > 1 or similar on an equivalent measure), finished with taxane-based chemotherapy treatment for at least 3 months, able to understand and comply with directions associated with testing and study treatments, and if they demonstrate postural control measurements outside of normative values (47). Participants are excluded from the study if they meet any of the following criteria: pre-existing vestibular disorders, history of motor deficits or neurological disease other than CIN-related, poorly controlled diabetes (HbA1c ≥ 8.0), non-ambulatory or lower extremity amputation (Note: assistive devices allowed), participating in physical or occupational therapy during the study (Note: engagement in additional therapies or physical activities (e.g. acupuncture) will be documented), or contraindicated to participate in unsupervised activity due to other issues (e.g. herniated vertebral disc).

We expect the study population to be representative of the demographics of the BC survivorship population in the United States between both sites. The CDC reports that 99% of BC cases occur among women and only 1% among men. The CDC census reports the rate of new BC cases in 2019 per 100,000 women by race as White/non-Hispanic 132.5, Black/non-Hispanic 128.4, American Indian and Alaska native/non-Hispanic 101.7, Asian and Pacific Islander/non-Hispanic 104.5, and Hispanic 101.9 (48).

### Recruitment and screening

This research opportunity is posted on public-facing websites including ClinicalTrials.gov (NCT06749210), Research Match, and Study Search to allow volunteers to self-refer by calling a dedicated medical center phone line or emailing the secure address [contact]. Further, advanced practice providers (APPs) refer eligible and interested clients to our research staff to complete screening. The study staff work onsite within the OSU SSCBC and Yale CBC outpatient facilities at least 2 days per week to follow up with volunteers and referring APPs. In addition, queries are run with electronic medical records (EMR) to identify potentially eligible clients of the OSU academic medical center system. Reports are generated using the criteria of a taxane-based chemotherapy plan being entered in the EMR and filtered by age (≥ 40 years) and prescribing physician. Through chart review, we identify the subset of clients who meet the study previously mentioned inclusion criteria. Researchers are provided with a list of potential recruits from a pharmacist on staff with SSCBC and Yale Cancer Center, which includes name, stage of breast cancer, whether they were exposed to taxane-based chemotherapy, and medical record number. Clinical research assistants then pre-screen participants from this list using the previously mentioned criteria.

For clients that meet the inclusion criteria, we request approval from the treating oncologist to contact the client for recruitment purposes. Eligible clients who are approved for recruitment by their oncologist are contacted by phone to inquire whether CIN symptoms persist and, if so, to determine interest and availability in participating in this study. Those able and interested are asked to schedule in-person screening of postural control, which involves attempting a short, but challenging balance task reported to distinguish fallers from non-fallers by Maki et al. (1994) (49). As previously reported (50), study volunteers stand quietly and bilaterally for 30 s on a balance plate (Bertec Corp, Columbus, OH) with eyes closed (QEC). Center of pressure (COP) variables of interest are calculated per Prieto et al. (1996) (51) and Roerdink et al. (2011) (52). Survivors are offered enrollment in the study if they demonstrate QEC postural control function that is outside of the estimated 70% confidence interval (CI) (47) of healthy, age-equivalent normative values in (1) COP ellipse area, (2) medial-lateral variability, (3) medial-lateral velocity or outside of the estimated 95% CI in terms of (4) COP complexity. Values corresponding to these inclusion thresholds are >400, >4.0, >11.0, <0.6, respectively.

### Adequacy of the potential participant pool

Between Yale and OSU, approximately 2300 new BC patients are seen annually (Yale n=1000, OSU n=1300), 500+ of whom will receive taxane-based cytotoxic chemotherapy annually. We conservatively estimate that approximately 50% of BC patients treated with cytotoxic chemotherapy will experience persistent CIN and measurable postural control deficits ([name] et al., 2018) yielding an eligible patient pool that grows by at least 113 BC survivors per site, per year. In addition to this annual presentation of new individuals with BC, both sites have established survivorship programs that serve thousands of BC survivors, including survivors not seen within our medical centers, who live with chronic CIN. Given the interest in non-pharmacologic options for survivorship treatment and lack of pharmacologic interventions to treat CIN (12), we anticipate screening 500 eligible individuals per year or 40 per month and enrolling up to 25% (i.e., 10 survivors per month) across sites.

Lastly, attending classes with an invited guest (dance partner) was found to affect engagement, by improving attendance of survivors (38). Therefore, we encourage participants to invite a partner to attend training sessions with them and for those who prefer not to invite from their social circle, we provide partners from a pool of talented university students within the relevant departments (e.g. Dance, Music, Health and Rehabilitation Sciences) at both sites to activate social engagement for enrollees randomized to the Tango experimental intervention.

### Interventions

The EXP intervention occurs over an 8-week period at a frequency of 2x per week with follow-up measures taken at 12 weeks. The CON intervention starts with 4-weeks of SOC and crosses over to experimental for the following 8 weeks at a frequency of 2x per week. No intervention session with accompanying data collection measures will last longer than 1.25 h total.

#### Codesign of Research Study Design and Intervention

Integration of patient lived experience and expertise was one of the key objectives for our group (53). Co-design is a meaningful, participatory collaborative process in research design and includes engagement of patient advocates within all stages of the research design and execution process (53). Early on in designing our interventional study, we reached out to our colleague patient advocate for input on the study planning phase. The PIs discussed the intent of the study and reached a shared collaborative understanding of the research question and how to best structure the clinical trial. Decisions at this stage were influential for all subsequent research processes. One of the central changes that occurred as a part of this discussion was shortening the waiting period from 8 weeks to 4 weeks for patients randomized to usual care. The reason for this change was based on careful deliberation of patient advocate input regarding how long survivors living with neuropathy can be expected to wait to receive potential relief through experimental intervention. Our prior work demonstrated relief from CIN dysfunction within 4 weeks of participation in the experimental intervention, therefore, we set the control wait period and primary outcome evaluation for both arms at 4 weeks (17).

#### Experimental Intervention: Tango

The Tango intervention will consist of 16 Adapted Argentine Tango (Adapted Tango) sessions over 8 weeks, adapted for individuals with mobility deficits by co-investigator (Co-I) [name] (30,54), further adapted for survivors with BC by lead principal investigator (PI) [name] (17), and taught by PI [name]. We aim to deliver a dose of skilled movement-to-music of at least 10 min and no more than 35 min per session, with breaks for water and rest offered at least every 10 min. Recommendations for implementation of Adapted Tango as a neurologic intervention focus on prevention of falls, use of implicit learning techniques to convey skilled movement goals, the structure of class (warm-up, lesson, cooldown), scaffolding and shaping lessons over time to establish competency in fundamentals, modifications deemed necessary for specific deficits, and music selection (30,54). Each song used within this intervention is from the tango genre with a single song duration of 1.5 to 8.5 min. Participants may sit or rest as needed during or between songs. Instructors ensure appropriate activity wear choices (e.g., footwear, breast support) and ensure qualified volunteers are present to partner with participants. Instructors complete 16 h of training with Co-I [name] as well as a certification exam to become qualified to teach the Adapted Tango technique. Volunteers who will partner participants for this study complete Co-I [name]’s 4 h Balance Management program plus an additional 3 h of training with PI [name] during which live instruction skills are evaluated by the PI before volunteers are cleared to partner participants.

The MPIs previously demonstrated that a Tango dose of about 20 minutes of movement-to-music is feasible for cancer survivors with postural control deficits to participate in at a rate of 2 times per week (17). To optimize factors mediating intrinsic motivation, instruction aims to achieve high Enjoyment and Perceived Competence among participants with low Pressure/Tension (55–57) as measured by IMI. We administer the IMI every 2 weeks to assess the achievement of these instructional goals. To assure integrity of the training, Co-I [name] assists MPIs [name] and [name] to monitor fidelity of the intervention. This subset of our team – two former professional dancers turned dance scientists and one oncology practitioner – monitor participant symptoms and training progression and troubleshoot any issues that arise through regular virtual meetings.

#### Control intervention with optional 1-way crossover: SOC with EXP

The active control intervention consists of 4 weeks of SOC, as prescribed by each participant’s medical oncologist. Within SOC, medical oncologists may prescribe pharmacologic treatments such as tricyclic antidepressants, anticonvulsants, and serotonin-norepinephrine uptake prohibitors (6,8,58). They may also recommend exercise and/or physical therapy (6). During the 4 weeks, clients are asked, weekly, to document their numbness/tingling due to CIN and any adverse events that occur via a smart phone application (i.e. the MyCap version of REDCap). After completion of outcomes assessments at the primary endpoint of 4 weeks, individuals in the CON arm will have the opportunity to cross over immediately to participate in the EXP tango intervention.

### Procedures/plans to ensure safety of interventions

Procedures to manage pain, functional guarding, inclement weather, seated interventional options and depression and anxiety monitoring are described in Lantis et al. (2023) (46).

### Outcome measure procedures and analysis

#### Primary outcome measures

##### Sensation (Aim 1):

We measure the impact of Tango on sensation using patient-reported outcomes (PROs) of “numbness/tinging/burning” via a validated 11-point Likert scale (59) that queries symptom severity in the prior 7 days. All surveys are administered through OSU’s instance of the REDCap database for in-person visits and through the REDCap phone application (MyCap) for data entry that participants perform remotely (e.g., SOC activity, follow-up period). Surveys are completed by the participants themselves with no data entry from staff. Answers are reviewed manually by authorized research collaborators, who prompt participants to complete or clarify answers as needed and document their responsibility for review from a list of authorized data reviewers.

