### Data management

Each study participant is assigned a unique six-digit identification number that cannot be traced to their protected health information. Participant data, coded using these identification numbers, are stored in a central database using REDCap. REDCap is a secure web-based platform that is designed for clinical trials which meets both HIPAA and 21 CFR. Clinical and biomechanical data are collected by study staff who input results into REDCap manually or via data upload. PRO data is manually entered into REDCap by study participants: participants undergoing the Tango intervention fill out questionnaires within REDCap before the start and at the end of each Tango session. SOC participants fill out questionnaires within MyCap, a mobile device application of REDCap once per week during the SOC wit period, for the purpose of adverse events reporting and symptoms tracking, then transition into the Tango intervention protocol in which they fill out questionnaires within REDCap before the start and end of each Tango session.

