### Adverse event monitoring and reporting

Participants randomized to the CON group are asked to report adverse events at the beginning of each week during the SOC period using the MyCap application, a mobile application version of REDCap that participants install on their smart phone devices. Once these participants engage in the intervention (one-way crossover period) they report adverse events on the same schedule as the EXP group. Participants randomized to the EXP arm complete adverse event reporting each time we see them (2x per week) via REDCap. With respect to the adverse event of falls, participants are asked about the incidence of falls and loss of balance. Researchers review REDCap responses once per week for the CON participants within the SOC period and prior to the start of Tango lessons for participants engaging in the Tango intervention (EXP and crossed over CON). If an adverse event is reported, the PI is notified. Classification of the events as Serious or not occurs within 24 hours.

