Neuropathy (primary outcome Aim 1)		x^†^		x	x	x	x	x
TUG-Cog (primary outcome Aim 2)		x		x	x	x	x	
CTCAE		x^†^		x	x	x	x	
Pain		x^†^		x	x	x	x	
Fatigue		x^†^		x	x	x	x	
GAD-2		x		x	x	x	x	
PHQ-2		x		x	x	x	x	
SF-36		x		x	x	x	x	
Satisfaction with intervention					x	x		
Activity outside of study tracking		x^†^		x	x	x	x	x
Intrinsic motivation					x	x		
Postural control during silence (QEC)		x^†^		x	x	x	x	
Postural control during music listening (QECm)		x^†^		x	x	x	x	
TUG		x		x	x	x	x	
TNSr+		x		x	x	x	x	
MiniBEST		x		x		x		
6mwt (EMG, IMUs)		x		x		x		
Upper extremity function		x		x	x	x	x	
Goal attainment (COPM)		x		x	x	x	x	
Blood-based biomarkers		x		x				
Cognitive load (EEG)		x		x	x	x	x	

† indicates a measure was repeated 3 times

**Table 3 T3:** SPIRIT report of within-session assessments. EMA refers to “Ecological Momentary Assessment”

Session Type	Baseline	Tango Intervetion		SOC (remote in MyCap app)
Timepoints	Before session start (Beg)	Before session start (Beg)	After completing session (End)	Weekly
ASSESSMENTS:				
Adverse events	x^a^	x^a^		
Neuropathy retrospective	x^a^	x^a^	x^b^	x^a^
PRO-CTCAE retrospective	x^a^	x^a^		x^a^
Pain retrospective (24 hours)	x	x		
Fatigue retrospective (24 hours)	x	x		
Neuropathy EMA	x	x	x	
CTCAE EMA	x	x	x	
Pain EMA	x	x	x	
Fatigue EMA	x	x	x	
Postural control during silence (QEC)	x	x		
Postural control during music listening (QECm)	x	x		
Activity outside of study tracking	x	x		x^a^
Satisfaction with session activity as neuropathy treatment			x	
Intrinsic motivation			x^c^	
COLLECTED TO FACILITATE TRIAL MONITORING AND INTERVENTION SHAPING:				
Rating of perceived physical exertion (RPE-P)			x^b^	
Rating of perceived mental exertion (RPE-M)			x^b^	

a Recall period = during the last week, since we last saw you, OR since you last answered these questions (whichever is the shortest time period)

b Recall period = during the activity just performed

c Queried every 2 weeks

**Table 4: T4:** EEG conditions

Condition	Description
Seated, eyes open	Resting data collected while seated. Participants will be instructed to watch a fixation point on a screen in front of them.
Quiet standing, eyes open	Participants will be instructed to stand with their eyes open while viewing a fixation point on a screen in front of them.
Quiet standing, eyes closed	Participants will be instructed to stand with their eyes closed.

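### The recall window for the Aim 1 primary item is stated in two incompatible ways, and the floating version could make recall differ by arm if session-level entries enter the primary model

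*Protocol article*

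**What the plan says.** The protocol article's Sensation (Aim 1) section defines the primary patient-reported outcome as numbness, tingling or burning, measured "via a validated 11-point Likert scale (59) that queries symptom severity in the prior 7 days". It names two collection routes for surveys: REDCap at in-person visits and the MyCap app for remote entry, with standard-of-care (SOC) activity given as an example of the latter.

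Table 3 has a row "Neuropathy retrospective", kept apart from the momentary (EMA) neuropathy row. Footnote a is attached to it at baseline, before each Tango session and in the weekly SOC column. The footnote sets recall to the last week, "since we last saw you, OR since you last answered these questions (whichever is the shortest time period". A second footnote, for the activity just performed, applies after each session.

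The entry schedules differ by arm. On EXP, the Interventions section states: "The EXP intervention occurs over an 8-week period at a frequency of 2x per week". Data management says participants in Tango "fill out questionnaires within REDCap before the start and at the end of each Tango session". On CON it states: "SOC participants fill out questionnaires within MyCap, a mobile device application of REDCap once per week", which covers the 4-week SOC period.

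Tables 1 and 2 schedule the Aim 1 primary outcome at baseline (repeated 3 times) and at week 4 in both arms, with no recall period shown. The Statistical analysis section makes the contrast of change from baseline to week 4 the primary estimand. Its longitudinal mixed model has fixed effects that include the baseline outcome and the session count inside each condition.

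**The concern.** One item cannot have both a fixed 7-day window and a floating window equal to the time since the last contact or entry. The floating rule also follows the contact schedule, and the contact schedule follows the arm. If entries made under it feed the primary comparison, EXP participants summarise roughly half a week while CON participants summarise up to a full week. A difference of this kind starts after allocation, so neither randomisation nor adjustment for the baseline score removes it.

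Baseline is affected as well. Footnote a covers the repeated baseline entries, which supply the model covariate and the stratification factor (score of at least 4 against below 4, Randomization section). If baseline visits fall less than a week apart, those scores also rest on less than 7 days. This is common to both arms, so it does not by itself bias the comparison. It does mean that a change score may subtract one window from another, and that the stratifier may not be the 7-day quantity the outcome section describes.

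**Working it through.** **1. The plan's own figure.** The Power calculations section gives SDs of 2.5 (control) and 1.9 (treatment), a target difference of 1.25, 50 completers per arm and a two-sided 5% test.

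- SE = sqrt((2.5² + 1.9²)/50) = sqrt(9.86/50) = 0.444
- Power = Φ(1.25/0.444 − 1.96) = 80.4% (79.6% with the noncentral t)

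The stated power of about 80% is reproduced and is not in dispute.

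**2. Recall windows under footnote a.**

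- EXP, two entries a week: 7/2 = 3.5 days on average, so min(7, 3 to 4) = 3 to 4 days
- CON during SOC, one entry a week: min(7, 7) = 7 days

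The nominal ratio is about 1:2. Both figures can move. A missed session lengthens the EXP window, up to 7 days. For CON, 7 days is a maximum, and the window is shorter if the week-4 visit comes less than a week after the last app entry.

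**3. Does footnote a reach the primary contrast?**

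- For: the footnoted row is the retrospective item, not the momentary one. The Sensation section mentions app entry during SOC for its surveys, and those entries appear in Table 3. The model has a session term. Nothing exempts week 4 from the footnote.
- Against: Table 3 is captioned as within-session, and Tables 1 and 2 schedule the week-4 value with no shortened recall.

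The documents leave this open.

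**4. Illustrative size.** The documents give no recall effect, so every shift below is an assumption.

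One simple mechanism is a score that equals the average over its window while symptoms fall linearly by 1.25 points over 28 days. Halving the window from 7 to 3.5 days moves its centre by 3.5 − 1.75 = 1.75 days. The shift is 1.25/28 × 1.75 = 0.08 point, in favour of EXP. Under this mechanism there is no shift if symptoms are flat. It matters under the null only if both arms decline alike.

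For a shift b, two-sided type I error = Φ(b/SE − 1.96) + Φ(−b/SE − 1.96). If b opposes a true effect of 1.25, power = Φ((1.25 − b)/SE − 1.96).

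| Assumed shift b (0–10 scale) | b / 1.25 | b / SE | Type I error | Power if b opposes benefit |
|---|---|---|---|---|
| 0.08 | 6% | 0.18 | 5.4% | 75% |
| 0.25 | 20% | 0.56 | 8.7% | 61% |
| 0.50 | 40% | 1.13 | 20.3% | 39% |

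**The case against.** The best defence is that Table 3 is not the primary-outcome schedule. Study Design lists it under tertiary measures, its caption refers to within-session assessments, and the Within-session effect section says these entries serve to evaluate the session. On that reading the week-4 item keeps the 7-day recall of the Sensation section, and the session and app entries are different variables. This is a fair reading, and it stands to the extent that a biased week-4 endpoint is not shown. It does not remove the conflict. Footnote a also covers baseline, and the session term leaves room for session-level scores in the model. Nor is this merely detail that a condensed article leaves to the full protocol: the article states two rules that disagree.

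A reader might infer three stronger things that the documents do not support:

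- **That mode of collection differs by arm at the endpoint.** EXP sessions are in person and SOC entries are remote. At week 4, however, Tables 1 and 2 give both arms TUG-Cog, balance-plate and EEG assessments, which need in-person contact. No difference in mode is shown at that visit.
- **That staff influence EXP answers in particular.** Reviewers of the surveys are people "who prompt participants to complete or clarify answers as needed", but this covers all surveys, on site or by app, in both arms. The same section says participants complete the surveys themselves, with no data entry by staff.
- **That the adverse-event schedule is part of the same defect.** It does differ by arm: "Participants randomized to the EXP arm complete adverse event reporting each time we see them (2x per week) via REDCap", against weekly app reports in CON during SOC. That is safety surveillance and has no bearing on the Aim 1 score.

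It is also fair that shifts of 0.25 to 0.5 point have no source in the documents, and that the simple mechanism above gives only about 0.08.

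**Conclusion.** The conflict in the recall rule is real and should be fixed. Session-level recall is nominally 3 to 4 days in EXP against up to 7 days in CON, and repeated baseline entries may also fall below 7 days. Whether this biases the primary contrast depends on two things the documents do not settle: whether footnote a governs the week-4 value, and whether session-level entries enter the primary model. Confidence that the primary comparison is affected is therefore moderate. The direction and size of any bias cannot be derived. The type I errors of about 5.4%, 8.7% and 20% are conditional on assumed shifts of 0.08, 0.25 and 0.5 point with 50 completers per arm, and they are not estimates for this trial. The stronger conclusion, that the arms are known to answer different questions at week 4, goes beyond the text.

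**What to change.** Reconcile the Sensation (Aim 1) section with Table 3, footnote a:

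- Use one fixed past-7-days stem for the primary item at baseline and at the week-4 assessment visit, in both arms, and state it in Tables 1 and 2.
- Base the primary baseline-to-week-4 contrast on these assessments only, and say so in the Statistical analysis section.
- Keep the session and app entries with the floating window as a separately named variable for within-session and descriptive use.
- Flag baseline and week-4 data already collected under the floating window, so that their effect can be examined.

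The cost is a change to the survey stem and the footnote, plus analysis wording. The downside is that session-level scores no longer contribute to the primary numbness and tingling model. The change is best made soon, because a recall window cannot be corrected once the answer is given. Enrollment opened in January 2025 and is expected to run to December 2028 (Trial status), so much of the data can probably still be collected under one stem.
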